# Yoga and breathing technique training in patients with heart failure and preserved ejection fraction: study protocol for a randomized clinical trial

**DOI:** 10.1186/s13063-018-2802-5

**Published:** 2018-07-28

**Keywords:** Yoga, Respiratory techniques, Heart failure with preserved ejection fraction, Randomized controlled trial, Autonomic system, Maximal inspiratory pressure, Maximal oxygen uptake

## Abstract

**Background:**

Current therapies for heart failure (HF) are followed by strategies to improve quality of life and exercise tolerance, besides reducing morbidity and mortality. Some HF patients present changes in the musculoskeletal system and inspiratory muscle weakness, which may be restored by inspiratory muscle training, thus increasing respiratory muscle strength and endurance, maximal oxygen uptake (VO_2_), functional capacity, respiratory responses to exercise, and quality of life. Yoga therapies have been shown to improve quality of life, inflammatory markers, and peak VO_2_ mostly in HF patients with a reduced ejection fraction. However, the effect of different yoga breathing techniques in patients showing HF with a preserved ejection fraction (HFpEF) remain to be assessed.

**Methods/design:**

A PROBE (prospective randomized open blinded end-point) parallel-group trial will be conducted at two specialized HF clinics. Adult patients previously diagnosed with HFpEF will be included. After signing informed consent and performing a pre-test intervention, patients will be randomized into three groups and provided with either (1) active yoga breathing techniques; (2) passive yoga breathing techniques (pranayama); or and (3) control (standard pharmacological treatment). Follow-up will last 8 weeks (16 sessions). The post-intervention tests will be performed at the end of the intervention period for analysis of outcomes. Interventions will occur continuously according to patients’ enrollment. The main outcome is respiratory muscular resistance. A total of 33 enrolled patients are expected. The present protocol followed the SPIRIT guidelines and fulfilled the SPIRIT checklist.

**Discussion:**

This trial is probably the first to assess the effects of a non-pharmacological intervention, namely yoga and specific breathing techniques, to improve cardiorespiratory function, autonomic system, and quality of life in patients with HFpEF.

**Trial registration:**

REBEC Identifier: RBR-64mbnx (August 19, 2012).

Clinical Trials Register: NCT03028168. Registered on 16 January 2017).

**Electronic supplementary material:**

The online version of this article (10.1186/s13063-018-2802-5) contains supplementary material, which is available to authorized users.

## Background

Several heart failure (HF) patients have limited physical activity due to early fatigue and dyspnea, which have been associated with low oxygen uptake and inspiratory muscle dysfunction, suggesting that physical deconditioning and respiratory muscle weakness might be underlying attenuated increased ventilation during hyperpnoea [1].

Over the last years, a reduced performance capacity has been associated with some additional factors that might be connected to the limited exercise response. Some studies have focused on the role of maximal inspiratory pressure (PI_max_) and inspiratory muscle endurance, which have been associated to low quality of life (QoL) and worse clinical prognosis [2–4]. In a randomized placebo-controlled trial with HF patients with reduced ejection fraction (HFrEF) and inspiratory muscle weakness (IMW), inspiratory muscle training markedly improved inspiratory muscle strength and endurance, incrementing submaximal and maximal functional capacity as well as QoL. In addition, heart rate variability (HRV) is also decreased by cardiovascular diseases and might result either from a direct central up-regulation of cardiovagal activity, or as a secondary effect of baroreceptor activation, or changes in respiration [5].

However, respiration has not been emphasized, despite evidence that breathing characteristics (rate and amplitude) markedly affect beat-to-beat cardiovascular variability [6–8]. Within this context, yoga breathing might combine abdominal, thoracic, and clavicular breathing phases in order to maximize breathing volume and therefore increase oxygen uptake. It has been reported that very and moderately slow yoga breathing creates a significant change in HRV frequency bands along and after exercise in healthy men and women [9, 10]. Recently, a study reported the comparative effectiveness of several forms of lifestyle modifications and found smoking cessation and yoga to be the most effective forms of cardiovascular disease prevention [11]. Furthermore, yoga techniques without breathing control have shown to improve oxygen uptake in patients showing HF, especially HFrEF [12]. However, even considering that almost half of HF patients show heart failure with preserved EF (HFpEF), few studies have been performed with such patients. It has been recently demonstrated that HFpEF induces significant molecular, mitochondrial, histological, and functional alterations in the diaphragm and soleus, which were attenuated by exercise training [13].

With respect to cardiovascular disease and aging, several authors have shown a significant reduction of HR variability in the frequency ranges associated with breathing by using spectral analysis of HR and respiration [14, 15]. Therefore, the present randomized clinical trial will be conducted primarily in order to test the hypothesis that an 8-week program of yoga and specific breathing techniques with various respiratory rhythms might be associated with improved inspiratory muscle responses. Secondly, changes in functional capacity, oxygen uptake efficiency slope, circulatory power, oscillatory ventilation, oxygen uptake kinetics in the recovery period, distinct features of the autonomic nervous system, natriuretic peptides, echocardiographic measurements, and QoL will be assessed in HFpEF patients, both with and without IMW.

## Methods/design

### Study design

A PROBE (prospective randomized open blinded end-point) parallel-group trial with three groups will be conducted at two specialized HF clinics (HF Clinic at Hospital de Clínicas de Porto Alegre (HCPA), RS, Brazil, and the HF ambulatory at Hospital ULBRA-Mãe de Deus, Canoas, RS, Brazil). The researchers will be divided according to their specific role in this study as (1) interveners – those performing the protocol interventions (blinded for outcomes, but not for groups); (2) medical appraiser – responsible for performing clinical tests (blinded for groups, but not for outcomes); and (3) analysts – those responsible for the statistical analyses (blinded for both groups and outcomes). The individuals will be instructed to avoid talking with the research team about protocol intervention and clinical trials.

### Inclusion and exclusion criteria

Adult patients aged from 45 to 75 years diagnosed with HFpEF, functional capacity class II and III, and who are being treated at a specialized HF clinic will be eligible. HF diagnosis will be established through medical history (signs and symptoms), echocardiographic findings (left ventricular ejection fraction ≥ 50%) [16], and medical records confirming management for HF.

Exclusion criteria are unstable angina, myocardial infarction, or cardiovascular surgery within the previous 3 months, active orthopedic or infectious disease, and treatment with steroids, hormones, or cancer chemotherapy. Additionally, pulmonary disease (forced vital capacity < 80% predicted and/or forced expiratory volume for 1 s < 70% predicted) [5, 17], significant mitral or aortic valve diseases, record of exercise-induced asthma, and active smoking will also be exclusion criteria. After selection, the discontinuous criteria are decompensated HFpEF, more than two consecutive absences in the intervention groups, and expressed willingness to discontinue at any time of the study.

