### Sample size

For sample size calculation, the higher the effect size and lower standard deviation in relation to the effect, the lower the sample size required to confirm the result. Thus, based on previous studies, the sample size was calculated using inspiratory muscle pressure as endpoint [18]. Considering a difference among treatments (effect size) of 15 cm H_2_O and a standard deviation (SD) of 12 cm H_2_O in the PI_max_, representing a 1.2 ratio (effect size/SD), using an α = 0.05 and power of 80%, nine patients would have to be included per group. In addition, considering a potential loss in patient follow-up of between 10% and 20%, the sample was set to 11 patients per group.

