#### Control group (standard pharmacological treatment)

Patients will be oriented to keep their pharmacological routine and daily activities with no structured exercises. They will have to return to the hospital for post-testing after 8 weeks of randomization. After final assessment, all patients, including those in the control group, will be invited to participate in the study breathing activities at the outpatient wards of this trial.

Intervention will last 8 weeks (16 sessions). The post-intervention tests will be performed at the end of the intervention period for the evaluation of endpoints (Fig. 2). To ensure security, data will be stored both in the main researcher’s and study coordinator’s computers, as well as being added to a virtual drive. Researchers, study coordinators, doctors, and statisticians will be allowed data access. Interventions will occur at specific facilities in HCPA (physiatrist sector) and in ULBRA University hospital (medical school) according to patient enrollment. Protocol deviation and adverse events involving individual participants in clinical studies in the HCPA are recorded in the strategic adviser system available in the hospital intranet. Deviations and adverse events occurring at ULBRA will be recorded in the same system as the HCPA. The auditing procedures will occur randomly or designated by the ethical committee for research analysis.

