### Statistical analysis

Initially, a descriptive analysis will be performed and data will be expressed as absolute and relative frequency, besides mean and standard deviation or quartiles, accordingly. The treatment groups will be compared using the generalized estimating equation, specific for repeated measurements, in order to compare the effects (means) across the three groups and the two times, in addition to the group × time interaction. The generalized estimating equation matrix of robust estimator covariance and exchangeable work correlation matrix will be used if normal distribution is found and will be analyzed by an identity binding function. In contrast, if an asymmetrical distribution is found, data will be analyzed using a gamma distribution linked to a logarithmic function. When significant, the factors under study will be compared by Bonferroni’s post-hoc test. Correlations will be described by the Pearson’s or Spearman’s test. The PASW18 (version 18.0, SPSS, Chicago, Illinois, USA) will be used in this analysis.

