### Trial status

This trial is currently in the patient selection and intervention stages. To date, 20 patients have been enrolled, 18 of whom have completed the trial.

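### One discontinuation criterion can apply only to the yoga arms, and the article does not keep discontinued patients for the week-8 tests or in the analysis

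*Protocol article*

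**What the plan says.** In the protocol article, the section on inclusion and exclusion criteria ends with a list that applies after selection: "the discontinuous criteria are decompensated HFpEF, more than two consecutive absences in the intervention groups". The third and last item on this list is the patient's own wish to stop, at whatever point it is voiced. The absence criterion names the intervention groups; the other two name no group.

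The yoga programmes run for 16 sessions over 8 weeks. Controls have no sessions, and their only stated obligation is the final visit: "They will have to return to the hospital for post-testing after 8 weeks of randomization".

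The sample size section raises nine patients per group to 11, "considering a potential loss in patient follow-up of between 10% and 20" per cent. It does not say which losses this covers or divide them by arm.

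The statistical analysis section plans a generalised estimating equation (GEE) to "compare the effects (means) across the three groups and the two times, in addition to the group × time interaction". The primary endpoint is PImax. The article names no analysis population and gives no rule for testing patients after discontinuation. The section on the HF clinics describes phone contact to support attendance at sessions and tests and to learn why patients were absent.

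**The concern.** Randomisation protects the comparison only while patients are measured and compared as allocated. A criterion based on attendance at sessions cannot be met before allocation and cannot be met by a control. If meeting it takes the patient out of follow-up, each yoga arm is reduced to those who kept attending, while the control arm is not filtered in this way. Decompensation is not specific to an arm, but it is an outcome-related reason for removal and its frequency may differ between arms.

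An analysis set can be defined later in a statistical analysis plan. A week-8 PImax that was never taken cannot be recovered by one. At the time of the article 20 of the 33 planned patients were enrolled, so 13 were still to come. Blinded assessment of the endpoint does not help, because the selection happens before the endpoint is measured.

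**Working it through.** **1. Does the rule act after randomisation, and in which arms?**
- Absences: need sessions, so they arise only after allocation and only in the active and passive yoga arms.
- Decompensation: any arm.
- Wish to stop: any arm.

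One of the three criteria is therefore specific to the yoga arms by construction.

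**2. Does discontinued mean out of the study, or only out of the sessions?** Three features point to leaving the study: the list stands with the eligibility criteria, the third item refers to the study and not to the sessions, and the sample size section describes losses as losses to follow-up. Against this, no sentence says that the post-test is omitted. Leaving the study is the more natural reading, but it is not explicit.

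**3. The plan's own allowance.** Inputs: nine per group, loss 10-20%, 11 per group.
- 9 / (1 - 0.10) = 10.0, so 10
- 9 / (1 - 0.15) = 10.6, so 11
- 9 / (1 - 0.20) = 11.25, so 12 (or 9 x 1.2 = 10.8, so 11)

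The step from nine to 11 is reproduced at about 15% loss, or at 20% by simple multiplication. It leaves room for two lost patients per arm (11 - 9 = 2). One patient is 1/11 = 9% of an arm and two are 2/11 = 18%. The nine is taken as given here.

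**4. Size of the bias if removed patients are not measured.** For a comparison of patients who have both tests:

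bias = fraction removed x gap,

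where the gap is how far the mean PImax change of those removed would have fallen below that of those kept. Both inputs are assumptions. The fraction borrows the plan's 10-20% range, and the gap is 0.5-1 of the plan's SD of 12 cm H2O, that is 6-12.
- Low: 0.10 x 6 = 0.6 cm H2O; 0.6/15 = 4% of the planned difference
- High: 0.20 x 12 = 2.4 cm H2O; 2.4/15 = 16%
- Gap of 0: bias 0

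**5. Cross-check by simulation.** Settings: 11 per arm, SD 12, no true effect, all controls kept, and the lowest-scoring yoga patients removed on a score that has correlation r with the outcome. Groups were compared by a two-sided t-test at 5%.

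| Removed from the yoga arm | r = 0 | r = 0.3 | r = 0.5 | r = 1 |
|---|---|---|---|---|
| 1 of 11: false difference (cm H2O) | 0.0 | 0.6 | 0.9 | 1.9 |
| 2 of 11: false difference (cm H2O) | 0.0 | 1.0 | 1.8 | 3.5 |
| 2 of 11: type I error | 4.9% | 5.5% | 6.3% | 11.4% |

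The same removal applied to controls as well brings the false difference back to about zero. The asymmetry is what produces the bias.

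**6. What the planned GEE does about it.** A patient with a baseline only supplies no observed change, but the exchangeable correlation still uses that baseline. With removal driven by baseline PImax alone (10-20% of one yoga arm, score correlated 0.5-1 with baseline, pre-post correlation 0.5-0.7, all assumed), simulation gave a group-by-time bias of only 0.0 to 0.3 cm H2O. A completers-only comparison of change gave -0.4 to -2.1, that is, against yoga. Material bias towards yoga therefore needs absence to be related to the PImax change that goes unobserved.

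**The case against.** The strongest reply is that the article is a condensed account. Analysis populations, intention-to-treat handling and missing-data rules are commonly left to the full protocol or analysis plan, and nothing in the statistical section excludes anyone. The phone contact should also limit both absences and missed tests. This stands in so far as the lack of a named analysis set is not itself the point. It does not dispose of the point, because the article does state a discontinuation rule, that rule differs between arms, and on its natural reading it ends data collection.

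Several stronger readings are tempting, and the documents do not support them:
- **Selected adherers against all controls.** Not so. Decompensation and the wish to stop can remove controls too. What controls do not face is selection on attendance.
- **The comparison is certainly biased towards yoga.** A reader might infer this from adherers being fitter. Being fitter at baseline is not enough, since the two-time GEE largely absorbs that. The direction depends on how absence relates to PImax change, and the article gives no data on this.
- **The rule uses up the loss allowance.** The sample size section does not say what its 10-20% covers, and it may already include these discontinuations.
- **Two patients have already been removed.** The trial status section reports "20 patients have been enrolled, 18 of whom have completed the trial", but the trial was still running, the other two may have been in treatment, and neither arm nor reason is given.

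A further fair objection is that week-8 testing of every patient regardless of clinical course would itself be a clinical rule, given that the test battery includes a treadmill test to volitional fatigue. Testing has to remain subject to the investigator's judgement.

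**Conclusion.** The concern holds in a limited form. The discontinuation criteria act after randomisation, one of them can be met only in the yoga arms, and the article does not keep discontinued patients for the week-8 tests or in the analysis. Followed as it reads, the rule may set yoga patients selected on attendance against controls with no such selection.

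The likely direction favours yoga if absence goes with a poorer PImax change. The illustrative size is 0.6-2.4 cm H2O, or 4-16% of the planned 15. It rests on an assumed 10-20% removal and an assumed gap of 6-12 cm H2O, and it is zero if absence is unrelated to PImax change. The planned GEE can give a somewhat different figure, because it also uses the baselines of patients without a post-test. The asymmetry between arms is certain from the text. That discontinued patients go unmeasured is the natural reading but is not explicit, and the size of any bias is an illustration.

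**What to change.** Leave the clinical criteria for stopping sessions as they are, and add four statements:

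1. Meeting a criterion ends the sessions and does not end study follow-up.
2. Every randomised patient who has not withdrawn consent for assessment is invited to the week-8 tests, at least to resting PImax, where the investigator judges testing appropriate.
3. All patients are analysed in their randomised group. The adherent set is shown only as a sensitivity analysis.
4. Discontinuations are reported by arm and by reason, including those that have already occurred.

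The cost is a short amendment and some week-8 visits by patients who stopped attending. The effect estimate may come out smaller, because non-adherent patients are then included. The change is worth most while patients are still being recruited, since it can secure only week-8 measurements not yet missed.

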### HF clinic and team approach

The two HF clinics participating in this trial are staffed by a multidisciplinary team of cardiologists, physical educators, physiotherapists, and nurses. On average, patients will start the protocols as soon as they conclude preclinical testing and will be randomized either to one of the intervention groups, or to the control group. In order to strengthen adherence to the study, the team will keep in touch by phone with the patients to reinforce their participation and confirm attendance at scheduled tests and interventions, or to understand the reasons for possible absences. Both centers have facilities that allow the performance of the yoga interventions described in the present study.

### Sample size

For sample size calculation, the higher the effect size and lower standard deviation in relation to the effect, the lower the sample size required to confirm the result. Thus, based on previous studies, the sample size was calculated using inspiratory muscle pressure as endpoint [18]. Considering a difference among treatments (effect size) of 15 cm H_2_O and a standard deviation (SD) of 12 cm H_2_O in the PI_max_, representing a 1.2 ratio (effect size/SD), using an α = 0.05 and power of 80%, nine patients would have to be included per group. In addition, considering a potential loss in patient follow-up of between 10% and 20%, the sample was set to 11 patients per group.

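### The stated inputs do not give nine patients per group for a two-sided comparison: 12 are needed, nine gives about 70% power, and the Bonferroni step is not allowed for

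*Protocol article*

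**What the plan says.** Protocol article, Sample size. The calculation uses maximal inspiratory pressure, which the Endpoints section names as primary. The inputs are: "Considering a difference among treatments (effect size) of 15 cm H_2_O" and "a standard deviation (SD) of 12 cm H_2_O in the PI_max", described as "representing a 1.2 ratio (effect size/SD". The result is "using an α = 0.05 and power of 80%, nine patients would have to be included per group". The allowance for loss follows: "considering a potential loss in patient follow-up of between 10% and 20%, the sample was set to 11 patients per group". The section does not say whether the test is one- or two-sided, which test was assumed, or whether 12 is the SD between patients at one visit or the SD of within-patient change.

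Protocol article, Statistical analysis. Generalized estimating equations (GEE) will be used "in order to compare the effects (means) across the three groups and the two times, in addition to the group × time interaction". Then: "When significant, the factors under study will be compared by Bonferroni’s post-hoc test". The number of post-hoc comparisons is not given, and no directional test is mentioned.

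**The concern.** An unqualified α of 0.05, placed beside a non-directional comparison of three groups, is normally read as two-sided. On that reading nine per group looks too few for a standardised difference of 1.25. The sample size also appears to rest on one two-group comparison at the full 5%, while the analysis has three groups and a Bonferroni step.

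This is the protocol's only power statement for its primary endpoint. If it is too favourable, a non-significant pairwise result could be given more weight as evidence against a difference than the design supports.

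**Working it through.** **Inputs.** From Sample size: difference 15, SD 12, α = 0.05, power 80%, nine per group, 11 after the allowance for loss. From Statistical analysis: three groups with Bonferroni post hoc. Assumed here because they are not stated: a two-sided test, and three pairwise comparisons (two are also shown).

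**Standardised difference.** 15 / 12 = 1.25. The protocol's 1.2 is this value truncated. Both values lead to 12 per group two-sided.

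**Reproducing the nine.** Two-sample t-test with noncentrality d·√(n/2) and 2n − 2 df. At n = 9 this is 1.25 × √4.5 = 2.652 with 16 df.

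- One-sided 5% (critical value 1.746): power 81.4%. Eight per group gives 76.8%, so nine is the one-sided answer.
- Two-sided 5% (critical value 2.120): power 70.2%. With d = 1.2 it is 66.7%.

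**Two-sided sample size.** Power is 75.3% at 10 per group, 79.6% at 11 and 83.3% at 12, so 12 are needed. The normal approximation is 2(1.960 + 0.842)² / 1.25² = 10.05, rounded up to 11. Taking error df from all three groups (3n − 3) gives 81.0% at 11. No two-sided two-group version gives nine.

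**With the planned comparisons**, d = 1.25:

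| Test | 9 per group | 11 per group |
|---|---|---|
| Two-sided 0.05, two-group df | 70.2% | 79.6% |
| Two-sided 0.05, pooled df | 72.0% | 81.0% |
| Bonferroni, 3 pairs (0.05/3 = 0.0167), two-group df | 50.8% | 62.8% |
| Bonferroni, 3 pairs, pooled df | 53.9% | 65.4% |
| Bonferroni, 2 comparisons (0.025), two-group df | 58.0% | 69.3% |
| Three-group F, one group 15 from both others | 73.2% | 82.9% |
| Three-group F, middle mean halfway | 59.9% | 70.4% |

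For 80% power with three Bonferroni pairs (two-group df), 15 per group are needed.

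**Loss to follow-up.** 11 × 0.80 = 8.8, which is below nine; 9 / 0.80 = 11.25, so 12. The largest loss that leaves nine of 11 is 1 − 9/11 = 18.2%.

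**What a baseline correlation would do.** Suppose 12 is a between-patient SD and rho is the baseline-to-week-8 correlation. The protocol gives no rho, so the values below are assumptions, at nine per group.

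- Baseline-adjusted analysis: effective d = 1.25 / √(1 − rho²), that is 1.443 at rho 0.5 and 1.750 at rho 0.7. Spending one df on baseline leaves 15 df (two groups) or 23 df (pooled). Power for three Bonferroni pairs is 65–68% at rho 0.5 and 83–86% at rho 0.7. Unadjusted for multiplicity it is about 82% at rho 0.5.
- Difference in change, which is what a group × time contrast measures: effective d = 1.25 / √(2(1 − rho)). With two-group df, unadjusted power is 56% at rho 0.3, 70% at 0.5, 79% at 0.6 and 89% at 0.7. With three Bonferroni pairs it is 36%, 51%, 62% and 76%.

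**The case against.** Several points on the other side have force.

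- **Sidedness is unstated, so nine is not strictly an arithmetic mistake.** This stands. The fault is that the figure depends on an undisclosed one-sided test, which does not match the non-directional three-group analysis.
- **The protocol never claims 80% power at a Bonferroni level.** This stands too. Bonferroni is a post-hoc step applied only after a significant result, and the number of comparisons is not given. A reader might infer that the trial's power simply is 51%. The documents do not support that: 51% needs three pairs and two-group df, and it becomes 54% with pooled df or 58% with two comparisons.
- **Two measurements per patient may raise power.** This also stands. A reader might infer that the trial cannot have 80% power. That goes too far, because the protocol does not say which SD 12 is, and a high correlation with a between-patient SD could reach 80%. But it states no correlation and claims no such gain. If 12 is already the SD of change, a change analysis gains nothing further; if it is between-patient and rho is below 0.5, the group × time contrast does worse than 70%.
- **A large-sample 2-df Wald test gives 78.8% at nine per group.** It does so only when one group lies 15 from both others, and it ignores the small-sample df. The F version gives 73.2%.
- **At the full 11 per group, unadjusted power is about 80%.** This is true, but the allowance for loss has then been used up in reaching the target.

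The 1.2 ratio and the shortfall of 8.8 against nine are small and would not justify a finding alone.

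**Conclusion.** The point holds in a limited form. Read as a two-sided two-group comparison, the protocol's own inputs require 12 per group; nine gives about 70% power, and 11 with no loss about 80%. The calculation also takes no account of the Bonferroni step: for three pairs, power is about 51–54% at nine per group and 63–65% at 11. Eleven per group covers up to 18% loss.

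These figures assume that 12 is the SD of the quantity compared, with no further gain from baseline. What is established is that the stated inputs and planned analysis do not support the stated 80%. It is not established that 80% is out of reach under every reading of the SD. The type I error and the effect estimate are unaffected.

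**What to change.** Keep 33 patients and correct the Sample size section:

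1. State that the test is two-sided and give the ratio as 1.25.
2. Replace the 80% claim with about 70% unadjusted and about 51–54% for three Bonferroni pairs at nine completers per group (about 80% and 63–65% at 11). State the number of comparisons assumed.
3. Alternatively, if a higher power is to be claimed, say whether 12 is a between-patient SD or an SD of change, name the analysis (baseline-adjusted or change), and give the correlation relied on with its source. Use the same df basis for every power quoted.
4. State that 11 per group covers up to 18% loss.

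The cost is wording only, with no extra patients. The stated power becomes less favourable unless a correlation can be justified. The Trial status section reports 20 patients enrolled and 18 completed, so the statement can still be corrected before results are reported.
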